There is an acute need to address maternal and child MI. Effective intervention strategies are necessary to simultaneously treat MI in mothers while preventing the development of MI in at-risk children [21]. Several efficacious psychological treatments are available for treating depression in adults, including cognitive behavioral therapy and dialectical behavior therapy administered via group psychotherapy [22, 23]. Group-based parenting programs teach parents skills to effectively manage difficult child behaviors and have been found to improve both parenting skills and child behavior problems [24]. However, there are currently limited programs available that support maternal mental health while concurrently aiming to improve parenting, called dual-generation interventions [3, 25]. Few programs have integrated interventions for both mothers and children, creating barriers (e.g., learning multiple therapeutic techniques) for mothers seeking support in both areas [26]. Skills and knowledge acquired in programs targeting maternal MI are often non-transferable to parenting contexts, and vice versa [27]. Emerging evidence has found that programs that simultaneously target maternal MI and parenting skills are up to 50% more effective than programs that target only one aspect [25, 27]. These findings demonstrate the long-term value of dual-generation interventions to magnify the positive effects of parental interventions on child mental health outcomes [3, 26–28].

In addition to increased efficacy, dual-generation programs may decrease barriers to participation for mothers of young children. Mothers attempting to access mental health and parenting interventions cite significant obstacles for engagement, such as requiring childcare, transportation, and time off work to attend programs [29–31]. Due to barriers such as these, maternal depression is widely undertreated; in Canada, only one third of mothers with depression or anxiety report receiving treatment [32]. By simultaneously treating depression and providing parenting support, barriers to participation in the intervention may be halved (e.g., requiring childcare once a week instead of twice).

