### Sample size {14}

A sample size of 180 participants will be sufficient to assess clinically meaningful reductions in both maternal depressive and child MI symptoms between groups. Based on the feasibility pilot data, we assume an effect size of *d* = 1.02 in improvement on maternal depression symptoms for both intervention groups (BRIDGE and DBT Skills-Only) [36]. A sample size of *n* = 60 per group will provide very high power (> 99%) to compare intervention groups to SAU. Based on pilot data on child MI symptoms, we assume a within-group SD of 13 on the CBCL and a mean improvement of 14 points [36]. As we anticipate little to no improvement in the SAU arm, we assume an effect size of* d* = 1.08 between BRIDGE and SAU and an effect size of *d* = 0.54 between BRIDGE and DBT-Only (i.e., an effect size 50% smaller than for BRIDGE, based on meta-analyses on the benefit of dual generation programs) [27]. A sample size of *n* = 60 per group will provide very high power (> 99%) to compare BRIDGE with SAU and adequate power (75%) to compare BRIDGE with DBT Skills-only.

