## Statistical methods

### Statistical methods for primary and secondary outcomes {20a}

Analyses for primary and secondary outcome variables, as well as exploratory outcome variables, will compare the changes over time between (a) the BRIDGE vs SAU groups and (b) BRIDGE vs DBT-only groups, each at *a* = 0.025 (combined type I error rate to 0.05). Linear models accounting for pre-intervention scores will be used as the primary analysis method. The persistence of effects at the 6-month follow-up will be examined using time-by-intervention interactions in a linear mixed-effects model, accounting for within-subject serial correlations and between-subject effects of the intervention and covariates. Standardized effect sizes for linear mixed models will be derived based on recommendations for linear mixed models [70, 71]. Standardized effect sizes of 0.20, 0.50, and 0.80 will be used to interpret small, medium, and large effects, respectively [70]. The research team will also investigate if there is baseline moderation by symptom severity to examine whether the BRIDGE intervention is more effective than the DBT-only or SAU interventions for participants who have higher symptom levels at pre-intervention.

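### The sample-size section and the background give incompatible accounts of the same cited evidence, and the 75% power for BRIDGE versus DBT on the CBCL holds under only one of them

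*Protocol article*

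**What the plan says.** All of the relevant text is in the protocol article.

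- **Sample size {14}.** For the CBCL, "we assume a within-group SD of 13 on the CBCL and a mean improvement of 14 points". With little or no change expected under services as usual (SAU), this gives d = 1.08 for BRIDGE versus SAU. For BRIDGE versus DBT-only the section uses d = 0.54, explained as "an effect size 50% smaller than for BRIDGE, based on meta-analyses on the benefit of dual generation programs" and supported by reference 27. With 60 per group it claims "adequate power (75%) to compare BRIDGE with DBT Skills-only".
- **Background and rationale {6a}.** Citing references 25 and 27, the protocol says that "programs that simultaneously target maternal MI and parenting skills are up to 50% more effective than programs that target only one aspect".
- **Statistical methods for primary and secondary outcomes {20a}.** BRIDGE is compared with SAU and with DBT-only, "each at *a* = 0.025". The primary method is a linear model that accounts for the pre-intervention score.

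**The concern.** Both sections rest on reference 27, but a program that is 50% more effective than its comparator is not a program whose comparator is 50% less effective. The first means a ratio of 1.5 and the second a ratio of 2. The sample-size section therefore credits BRIDGE with a 100% advantage over DBT, where the background allows at most 50%.

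Child symptoms are a primary outcome, superiority of BRIDGE over DBT on them is a stated hypothesis, and this contrast is the one that isolates the contribution of the parenting component. It is also the only contrast in the sample-size section whose claimed power is not above 99%, so it is the one where a change in the assumed effect matters.

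**Working it through.** **Inputs**

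- BRIDGE versus SAU: 14/13 = 1.08 (Sample size {14}).
- 60 analysed per arm (Sample size {14}).
- Alpha 0.025 per comparison (Statistical methods {20a}). Sidedness is not stated. Two-sided is assumed because it reproduces the protocol's figure.
- No dropout allowance, as in the protocol.

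**Step 1: reproduce the stated power**

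Noncentrality = d × √(n/2) = 0.54 × √30 = 2.958. The two-sided 0.025 normal critical value is 2.241.

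- Normal approximation: Φ(2.958 − 2.241) = 76.3%.
- Noncentral t, 118 df: 75.3%.

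This matches the stated 75%. Two-sided 0.05 (or one-sided 0.025) gives 83–84%, and two-sided 0.0125 gives 66–68%, so neither of those is what was used.

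**Step 2: convert each description to a BRIDGE–DBT difference, keeping BRIDGE at 1.08**

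| Description | DBT effect | Difference | BRIDGE ÷ DBT | Difference in CBCL points (SD 13) |
|---|---|---|---|---|
| Sample size: 50% smaller | 1.08 × 0.5 = 0.54 | 0.54 | 2.0 | 7.0 |
| Background: up to 50% more effective | 1.08/1.5 = 0.72 | at most 0.36 | at most 1.5 | 4.7 |

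It makes no difference whether the halving in the sample-size section applies to DBT's own effect or to the contrast between the arms. Since 1.08 − 0.54 = 0.54, both readings give the same figure.

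**Step 3: power at d = 0.36**

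Noncentrality = 0.36 × √30 = 1.972.

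- Normal approximation: Φ(1.972 − 2.241) = 39.4%.
- Noncentral t: 38.6%.

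The number per arm needed for 75% power is 2 × (2.241 + 0.674)²/d². This is about 132 at d = 0.36, against 59 at d = 0.54.

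**Step 4: credit for baseline adjustment**

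If 13 is the unadjusted SD, adjusting for the pre-intervention score raises the effective d to d/√(1 − r²), where r is the pre-post correlation. The protocol gives no value for r, so those below are assumptions.

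| r | Effective d from 0.36 | Power | Power from 0.54 with the same credit |
|---|---|---|---|
| 0 (unadjusted) | 0.36 | 38.6% | 75.3% |
| 0.3 | 0.377 | 42% | 80% |
| 0.5 | 0.416 | 50% | 87% |
| 0.7 | 0.504 | 69% | 97% |

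To bring 0.36 back up to an effective 0.54 requires √(1 − r²) = 0.36/0.54 = 2/3, that is r = √(5/9) ≈ 0.75. The stated 75% is reproduced without any such credit.

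**The case against.** The strongest reply is that nothing in the sample-size section is miscalculated. Half of 1.08 is 0.54, and 0.54 gives 75%. That is correct: the issue is the input and its justification, not the power calculation.

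A reader might go further and infer that the sample-size section misconverted its source and that the trial's true power for this contrast is 39%. The document does not support that. The background sentence is general, cites two references, and names neither an effect metric nor whether the outcome is maternal or child. The sample-size statement is the more specific one and relies on reference 27 for the child outcome. The upper figure in the background could come from reference 25. Neither source is available here, so which section misdescribes the evidence is open.

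Treating 0.36 as a firm upper bound also goes too far. The background compares dual-focus programs with any program that targets a single aspect, which may include parenting-only programs. The comparator here is a maternal program with no parenting content, judged on a child outcome. The bound holds only if the general figure carries over to this contrast and is a ratio of standardized effects.

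The planned baseline adjustment also has to be allowed for. It makes a single 39% too bare, but it does not restore 75% at the correlations tried.

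Lower figures of 33–35% can be obtained by reducing the arms to 52–55 using the pilots' retention. They should not be relied on. The 92.3% in the telehealth pilot describes program completion, not outcome completion, and the protocol plans an intention-to-treat analysis with maximum likelihood for missing data. Nor does the protocol say that a non-significant result would be read as showing no added benefit.

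What remains after all of this is that two statements citing the same reference cannot both be right, and the claim of adequate power depends on the more favourable one.

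**Conclusion.** The point holds as an inconsistency with a conditional consequence. The two sections imply BRIDGE–DBT differences of 0.54 and at most 0.36, and the stated 75% is obtained only with 0.54. If the background statement is the accurate one, power is about 39% unadjusted and about 42–69% with baseline adjustment at assumed correlations of 0.3 to 0.7.

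Those figures assume that the background reports reference 27 correctly, that its percentage is a ratio of effects on the d scale and applies to this contrast, that BRIDGE versus SAU stays at 1.08, that the test is two-sided at 0.025, and, for the adjusted figures, that 13 is the unadjusted SD. If reference 27 in fact reports a halving, 0.54 and 75% can stand and the background is the text in error. The contradiction itself depends on none of these assumptions about power.

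**What to change.** Check what reference 27 reports for child outcomes, then bring the two sections into line.

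- **If the background wording is right:** in Sample size {14}, give the expected BRIDGE–DBT effect as no more than about 0.36. Replace the claim of adequate power at 75% with the lower figure, or show power over d = 0.36 to 0.54 with any correlation assumption stated. Describe 0.54 as the difference detectable with 75% power rather than the one expected.
- **If the source reports an effect half as large for single-focus programs:** keep 0.54 and correct the sentence in Background and rationale {6a}.

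Either way this is a change of text. It requires no extra participants and no change to the analysis. In the first case the cost is a less favourable power statement for one primary-outcome contrast.

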Two pilot studies have been conducted to evaluate BRIDGE [35, 36]. In a pre-post feasibility study, mothers with depression (*n* = 28) completed an in-person, 16-week trial of BRIDGE [36]. The intervention demonstrated good feasibility, with high retention (86% retention) and significant reductions in maternal depression (*d* = 1.02) and child MI (*d* = 1.08). In focus groups conducted at post-test, participants indicated that they were generally satisfied with the program [36]. Mothers expressed that they found the parenting skills complementary to the DBT skills, with one participant stating, “Because I understood the DBT language… it made it easier for me to understand it when we did it with children and the way it applies is just amazing.” In compliance with public health recommendations to reduce in-person contact and physical distance during the COVID-19 pandemic, a second pilot study was run to evaluate the efficacy of BRIDGE delivered via telehealth using asynchronous psychoeducational videos alongside synchronous weekly group sessions [35]. Participants (*n* = 39) showed significant reductions in child MI symptoms (*d* = 0.41), maternal depression (*d* = 1.13), and parenting stress *(d* = 0.39) from pre- to post-intervention [35]. Retention was high, with 92.3% of mothers completing the program [35]. Given these favorable results, further research comparing BRIDGE to other available programs is necessary to expand services to mothers in need.

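### The 75% power for BRIDGE versus DBT-only on child symptoms requires T2 data from all 60 mothers per arm; no loss is allowed for, and at the pilots' loss rates the same calculation gives about 68–71%

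*Protocol article*

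**What the plan says.** The section Sample size {14} gives a total of 180 participants, 60 per group. For the child outcome, the text reads "we assume a within-group SD of 13 on the CBCL and a mean improvement of 14 points", which yields d = 1.08 for BRIDGE versus services as usual (SAU). For BRIDGE versus DBT-only it takes d = 0.54, described as "an effect size 50% smaller than for BRIDGE, based on meta-analyses on the benefit of dual generation programs". With 60 per group it concludes that there is "adequate power (75%) to compare BRIDGE with DBT Skills-only".

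Statistical methods for primary and secondary outcomes {20a} tests two comparisons, BRIDGE versus SAU and BRIDGE versus DBT-only, each at "0.025 (combined type I error rate to 0.05"). It names linear models that account for the pre-intervention score as the primary analysis. Outcomes {12} defines the primary endpoints as change from pre- to post-intervention, so the T2 questionnaire is needed.

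Background and rationale {6a} reports the two pilots: the in-person study (n = 28) "with high retention (86% retention"), and the telehealth study (n = 39) "with 92.3% of mothers completing the program". The sample size section takes its effect sizes and SD from the in-person pilot but does not mention retention in either pilot.

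**The concern.** The same 60 per group serves as the number of participants and as the number analysed. That is consistent only if nobody is lost before T2, which the article gives no reason to expect: T1 falls about 8 weeks before the intervention starts, T2 is at week 25, and both pilots lost mothers.

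The comparison affected is the one that matters most for interpretation. BRIDGE versus DBT-only is the contrast that isolates the benefit of adding parenting support, and it is the only one whose stated power is not far above 90%. If it came out null, readers would judge that result against a stated power of 75% labelled adequate, when on the same inputs and with ordinary loss the figure would be lower.

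**Working it through.** **Inputs**
- Effect size: 14/13 = 1.08 for BRIDGE versus SAU; half of that is 0.54 for BRIDGE versus DBT-only (Sample size {14}).
- Alpha: 0.025 per comparison ({20a}). Sidedness is not stated; two-sided is assumed because it reproduces the stated figure.
- Arm size: 60, with 1:1:1 allocation (Sample size {14}; Sequence generation {16a}).
- Loss: 100 − 92.3 = 7.7% (telehealth pilot) and 100 − 86 = 14% (in-person pilot), from {6a}. Using these as T2 loss in both arms is an assumption.

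**Formula.** Two-sample t test with n analysed per arm: degrees of freedom 2n − 2, noncentrality δ = d × √(n/2), power = P(|T| > critical value) under the noncentral t distribution.

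**Reproducing the stated figure.** n = 60: δ = 0.54 × √30 = 2.958, df = 118, critical value 2.270, power **75.3%**. The normal approximation gives 76.3%. Other alpha levels do not fit: two-sided 0.05 gives 83.5% and two-sided 0.0125 gives 66.3%. So the 75% is an unadjusted comparison at two-sided 0.025 with all 60 per arm analysed.

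**The same calculation with loss**

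| T2 loss in both arms | n per arm with T2 | δ | Power (t) | Power (normal) |
|---|---|---|---|---|
| none | 60 | 2.958 | 75.3% | 76.3% |
| 7.7% | 60 × 0.923 = 55.4 | 2.842 | 71.5% | 72.6% |
| 14% | 60 × 0.86 = 51.6 | 2.743 | 68.0% | 69.2% |

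In whole numbers, 55 per arm gives 71.1%, 52 gives 68.4% and 51 gives 67.4%. Against the reproduced 75.3%, the drop is about 4 points at 7.7% loss and about 7 points at 14%.

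**Randomised numbers that would leave 60 with T2 data.** 60/0.923 = 65.0, just above 65, so 66 per arm (198 in total); 60/0.86 = 69.8, so 70 per arm (210 in total).

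**SAU comparisons.** At 51.6 per arm, power is 99.8% for d = 1.02 and 99.9% for d = 1.08, so the statements of more than 99% survive the larger loss.

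**Possible offset from baseline adjustment.** If 13 is the SD of raw scores, adjusting for the T1 score with baseline–T2 correlation r raises the effective effect size to 0.54/√(1 − r²). The article gives no r, so these values are assumptions:

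| r (assumed) | Effective d | Power at 55.4 per arm | Power at 51.6 per arm |
|---|---|---|---|
| 0 | 0.540 | 71.5% | 68.0% |
| 0.3 | 0.566 | 75.9% | 72.5% |
| 0.5 | 0.624 | 84.2% | 81.2% |

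**The case against.** **The sentence contains no arithmetic slip.** True: 60 per group does give 75%. The fault lies in applying that figure to a trial of 180 participants without any loss.

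**The 180 might mean T2 completers.** Interim analyses {21b} puts the mid-way point at about 90 mothers who have completed T2, which would fit 180 completers. But the abstract and the sample size section call the 180 participants, and nothing in the article says that more will be randomised. The interim wording fits equally well with treating participants and completers as the same number.

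**The pilot figures are not T2 response rates.** This stands. One is programme completion and the other an unspecified retention, both in single-arm BRIDGE cohorts, so neither informs loss in the DBT arm. Mothers who stop treatment remain in the intent-to-treat analysis and may still answer T2, which is paid. The 86% comes from in-person delivery; the telehealth pilot is the closer match. These are nonetheless the only retention figures in the article, and on the unadjusted calculation any loss reduces the power.

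**Maximum likelihood keeps everyone in.** A mother with only a baseline score stays in the model but adds almost nothing to the T2 contrast. Observed follow-up data could recover a little in the mixed model.

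**Baseline adjustment may make up the loss.** This also stands as a possibility, as the second table shows. It limits what can be concluded. A reader might infer that the trial's true power is below 75%. The article does not support that: it does not say whether 13 is a raw-score or change-score SD, and it gives no correlation, so the power of the planned analysis could be below or above 75%.

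**Conclusion.** The point holds as a statement about the published power figure. On the protocol's own unadjusted inputs, 75% requires complete T2 data from both arms, and no allowance for loss is stated. With T2 loss of 7.7% in both arms the figure is about 71%; with 14% it is about 68%. The first is the better guide because that pilot was delivered by telehealth, as this trial is.

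The range rests on three assumptions: a two-sided test, pilot retention carried over as T2 loss in both arms, and no gain from baseline adjustment. The shortfall is moderate, roughly 4 to 7 points on a figure already below 80%. It does not show that the design is invalid or that 180 is the wrong number, and the SAU comparisons are unaffected.

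**What to change.** Keep n = 180. Restate the power for BRIDGE versus DBT-only at the number of mothers expected to have T2 data: about 68–71% at d = 0.54 with 8–14% loss, on the protocol's unadjusted inputs, with the loss rate labelled as an assumption. Drop or qualify the word adequate.

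If the sponsor counts on baseline adjustment to recover power, state whether the SD of 13 is for raw or change scores, give the assumed baseline–T2 correlation, and report the power on that basis. If 180 was meant as the number with T2 data, say so and give the number to be randomised.

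The cost is a sentence or two and, on the unadjusted inputs, a less favourable figure. No extra participants and no change to the analysis are needed, and the statements of more than 99% power against SAU can stay.

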### Recruitment {15}

Recruitment will occur online through multiple sources including online advertisements posted to various social media platforms including the Hearts and Minds Facebook, Instagram, and Twitter accounts. Recruitment materials will also be provided to community agencies, healthcare facilities, and childcare centers. Individuals who meet all eligibility criteria and consent to randomization will be invited to participate. Eligible participants will receive compensation of up to $200 CAD for engaging with the study for its entire duration. This includes a $25 CAD honorarium for completing the pre-program questionnaires, $25 CAD for completing the optional pre-program Zoom assessment, $50 CAD for completing the post-program questionnaires, $50 CAD for the optional post-program Zoom assessment, $25 CAD for completing the follow-up questionnaires, and an additional $25 CAD for participants in the BRIDGE condition who complete at least 75% of the weekly surveys.

### Assignment of interventions: allocation

#### Sequence generation {16a}

Participants will be randomly allocated in a 1:1:1 ratio to the BRIDGE intervention, DBT-Skills intervention, or SAU. Stratified randomization will be applied based on (a) participants’ availability for virtual therapy timeslots (i.e., lunchtime or evening group) and (b) province of residence. Randomization will occur in blocks to ensure approximately equivalent group sizes.

#### Concealment mechanism {16b}

A statistician who is not affiliated with the BRIDGE clinical research team will create the allocation table. Next, a REDCap administrator, who is not affiliated with the BRIDGE clinical research team, will upload the randomization lists to Redcap and finalize the project. The REDCap randomization module ensures that once the REDCap project is finalized, no changes to the randomization tables can be made. Therefore, the allocation sequence will be concealed from all personnel affiliated with the BRIDGE clinical research team until interventions are assigned.

#### Implementation {16c}

Randomization will be conducted using the REDCap randomization module [37, 38]. Randomization lists will be uploaded to REDCap prior to the first randomization block and will not be changed throughout the project’s duration. Following the completion of baseline questionnaires, a BRIDGE research assistant will notify participants of their treatment condition based on the computer-generated assignment.

